#### Recruitment

As of February 2020, 2136 IUSMM patients have been enrolled in the Signature Bank since the year 2012, including 822 individuals with psychotic disorders, and 853 with anxiety and/or mood disorders. The study was approved by the local ethics committee in accordance with the Declaration of Helsinki, and the Signature Bank’s management framework provides further details on recruitment and consent forms. Between August 26, 2019, and February 26, 2020 (6 months), a preliminary validation study [100] allowed us to recruit 93 of the Signature Bank participants diagnosed with either psychotic disorders, or with anxiety and mood disorders. In total, 36 were female (39%) and 57 were male (61%). They further completed the Recovery Assessment Scale and Citizenship Measure, both of which a 5-point Likert scale was used to rate items. For the former, the mean was 3.77 (out of 5; SD 0.78). For the latter, the mean was 3.91 (out of 5; SD 0.63). The type of participants we need can thus easily complete our questionnaires in parallel to those of the Signature Bank. A research assistant with lived experience of an MHPI will contact by phone all the above-mentioned 93 Signature Bank participants who have already been in touch for the previous validation study and who have already accepted to be contacted again by our team for such purposes. If needed, other Signature Bank participants who meet the inclusion criteria will also be contacted until 30 Information and Consent forms are returned. The Information and Consent form will be sent by email to those who provide an email address. They will be offered CA$20 as compensation indemnity for the baseline and follow-up completions of the Recovery Assessment Scale, the Citizenship Measure, and the Bem Sex Role Inventory (see the *Sex and Gender* section).

#### Quantitative Analyzes

Baseline characteristics will be summarized, including for the measures of clinical recovery (see the *Outcome Measures at Follow-up* section), the Recovery Assessment Scale, the Citizenship Measure (personal-civic recovery), the COVID-19 Stress Scales, and the Bem Sex Role Inventory. All participants with data at baseline (T1) and follow-up will be included in the analyses. We will compare within-patient change from baseline to intervention versus control group in the study outcome measures using the Student paired sample *t* test. The analysis will run on intervention and control practices separately so as to explore practice level impact on the differences in outcomes. Comparison of confidence interval and effect size between groups will be assessed.

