**Methods:**

PSWs will lead a typical informal peer support group within the larger context of online peer support groups, focusing on personal-civic recovery. They will be scripted with a fixed, predetermined duration (a series of 10 weekly 90-minute online workshops). There will be 2 experimental subgroups—patients diagnosed with (1) psychotic disorders (n=10) and (2) anxiety or mood disorders (n=10)—compared to a control group (n=10). Random assignment to the intervention and control arms will be conducted using a 2:1 ratio. Several instruments will be used to assess clinical recovery (eg, the Recovery Assessment Scale, the Citizenship Measure questionnaire). The COVID-19 Stress Scales will be used to assess effects in terms of clinical recovery and stress- or anxiety-related responses to COVID-19. Changes will be compared between groups from baseline to endpoint in the intervention and control groups using the Student paired sample t test.

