#### Outcome Measures at Follow-up

The COVID-19 Stress Scales (36 items) and the measures of personal-civic recovery (47 items) will be repeated, along with the following measures of clinical recovery, which are routinely collected among all Signature Bank participants:

Anxiety: Anxiety State-Trait Anxiety Inventory Form Y6, 6 items (STAI-Y6) [93];Depression: Depression Patient Health Questionnaire, 9 items (PHQ-9) [94];Alcohol dependence: Alcohol Use Disorders Identification Test, 10 items (AUDIT-10) [95];Drug dependence: Drug Abuse Screening Test, 10 items (DAST-10) [96];Psychosis: Psychosis Screening Questionnaire, 12 items (PSQ) [97]; andSocial functioning: WHO Disability Assessment Schedule, 12 items (WHODAS 2.0) [98].

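### Outcomes are compared as raw change with no conditioning on the T1 score, which loses precision at moderate T1–T2 correlation and lets part of any chance baseline imbalance into the observed effect

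*Protocol article*

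**What the plan says.** The 'Quantitative Analyzes' section of the protocol article sets the outcome analysis: "We will compare within-patient change from baseline to intervention versus control group in the study outcome measures", with the Student paired sample t test as the method. The Abstract says the same: "Changes will be compared between groups from baseline to endpoint in the intervention and control groups using the Student paired sample t test". The section adds that "The analysis will run on intervention and control practices separately" and that "Comparison of confidence interval and effect size between groups will be assessed".

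The T1 score is available throughout. 'Outcome Measures at Follow-up' states that "The COVID-19 Stress Scales (36 items) and the measures of personal-civic recovery (47 items) will be repeated", together with the routine clinical recovery scales. Having a T1 score is a condition of entry to the analysis: "All participants with data at baseline (T1) and follow-up will be included in the analyses". Apart from forming the change score, its only stated use is descriptive: "Baseline characteristics will be summarized, including for the measures of clinical recovery". The sex-stratified analyses and gender-role correlations under 'Sex and Gender' do not condition on it either.

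**The concern.** Subtracting T1 from T2 treats the baseline coefficient as exactly 1. With equal variances at the two times, the regression slope of T2 on T1 is rho, which is below 1. Two things follow. The change score carries more noise than a baseline-adjusted outcome unless rho is very high. And an arm that happens to start lower is expected to gain more even if the intervention does nothing.

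This matters because the control arm is planned at 10 (5 per diagnosis), so sizeable chance imbalance is likely. Under 'Principal Research Questions' the study is meant to detect an effect attributable to peer support and to supply data for a later randomised trial. The Discussion would attribute significant between-group differences to the intervention. An effect estimate carried forward on that basis should not be wider, or more dependent on the baseline draw, than the collected data require.

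**Working it through.** The article states no power, alpha, target effect or sample-size calculation, so there is no figure to reproduce.

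**Inputs from the article**
- Arms 20 v 10, and 10 v 5 within each diagnosis ('Allocation').
- T2 completers 7 + 10 = 17 experimental v 7 control (Table 1).
- Recovery Assessment Scale: "For the former, the mean was 3.77 (out of 5; SD 0.78". Citizenship Measure SD 0.63 (same section, 'Recruitment').

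**Assumptions**
- rho is not given and is varied from 0.3 to 0.9.
- SDs are equal at T1 and T2, and participants are independent.
- The arms are contrasted by a two-sample comparison of changes. The plan does not name such a test; this is the nearest valid reading of the comparison it intends.

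**Formulas**, with c = √(1/n1 + 1/n2) and N = n1 + n2
- Variance of the effect from change scores: SD² × 2(1 − rho) × c².
- Variance with T1 as covariate: SD² × (1 − rho²) × [1 + 1/(N − 4)] × c². The bracket is the small-sample price of estimating the slope; at N = 30 it is 27/26.
- Standard error (SE) of the chance baseline difference: SD × c. Share passing into the change-score effect: 1 − rho, in favour of the arm that started lower.

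**Results at 20 v 10.** c = √(0.05 + 0.10) = 0.387, so the SE of the baseline difference is 0.78 × 0.387 = 0.302 points on the Recovery Assessment Scale and 0.63 × 0.387 = 0.244 on the Citizenship Measure. For the Recovery Assessment Scale:

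| rho | 2(1 − rho) | (1 − rho²) × 27/26 | Variance ratio | SE, change | SE, adjusted | Shift from a 1-SE imbalance |
|---|---|---|---|---|---|---|
| 0.3 | 1.40 | 0.945 | 1.48 | 0.357 | 0.294 | 0.21 |
| 0.5 | 1.00 | 0.779 | 1.28 | 0.302 | 0.267 | 0.15 |
| 0.7 | 0.60 | 0.530 | 1.13 | 0.234 | 0.220 | 0.09 |
| 0.8 | 0.40 | 0.374 | 1.07 | 0.191 | 0.185 | 0.06 |
| 0.9 | 0.20 | 0.197 | 1.01 | 0.135 | 0.134 | 0.03 |

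The 95% CI half-width at rho 0.5 is 0.62 points with change scores and 0.55 with adjustment; at rho 0.8 it is 0.39 and 0.38. On the Citizenship Measure a 1-SE imbalance shifts the effect by 0.12, 0.07 and 0.05 points at rho 0.5, 0.7 and 0.8.

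**At the 17 v 7 completers**, the SE of the baseline difference on the Recovery Assessment Scale is 0.350 points, and the variance ratio is 1.27, 1.12 and 1.06 at rho 0.5, 0.7 and 0.8.

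**Break-even.** Setting the two variances equal gives rho = 2(N − 4)/(N − 3) − 1:
- 20 v 10: 52/27 − 1 = 0.93.
- 17 v 7: 40/21 − 1 = 0.90.
- 10 v 5: 22/12 − 1 = 0.83.

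Above these values adjustment is slightly the less precise.

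**Simulation check** (40,000 trials per setting). At 20 v 10 the variance ratios were 1.287 (rho 0.5) and 1.137 (rho 0.7). The slope of the change-score effect on baseline imbalance was −0.50, −0.30 and −0.20 at rho 0.5, 0.7 and 0.8; with adjustment it was about 0.

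**The case against.** **The plan names a different test.** A paired t test run separately by arm, followed by a comparison of intervals and effect sizes, contains no two-sample test of changes. This stands. The figures above describe what would remain after that larger fault was repaired in the simplest way. They are not the operating characteristics of the named test. The point still survives: swapping in a two-sample test of changes would leave T1 unused as a covariate.

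**This is efficiency, not bias.** A reader might infer that change scores bias the result or inflate the false-positive rate. They do neither: over repeated randomisation the estimator is unbiased and its two-sided type I error is 5%. In simulated null trials at 20 v 10 and rho 0.5, a false benefit arose in 8.9% of those where the experimental arm started at least 1 SE lower (2.4% with adjustment, nominal 2.5%). That is offset by about 0.2% when the experimental arm starts correspondingly higher. The problem is conditional on the allocation obtained.

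**rho may be high.** Under 'The Citizenship Measure', respondents rate both primary scales for the period since the pandemic began, so the T1 recall window (August, Table 2) lies inside the T2 window (November). The article also reports very good test-retest reliability for the Recovery Assessment Scale. On the other side, subscale alphas of 0.65 to 0.86 (Recovery Assessment Scale) and 0.60 to 0.74 (Citizenship Measure) suggest measurement error that would hold rho down, although full-scale reliability may be higher. None of this fixes rho, so the 28% at rho 0.5 should not be read as the expected gain.

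**Adjustment is not free at every rho.** This stands. In the 10 v 5 comparisons at rho 0.9 the variance ratio is 0.965, against adjustment.

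**This is a feasibility study, and an article may leave covariates to a fuller plan.** No power target is missed, and the effect-size calculation is not spelled out. But the scale of comparison is stated twice as change from baseline, so this is a stated choice rather than a gap.

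**Conclusion.** The concern holds as a matter of precision and of sensitivity to chance imbalance, not as a claim of bias or invalid inference. Under equal variances, independent participants and a two-sample comparison of changes at 20 v 10, not conditioning on T1 inflates the variance of the effect by about 48% at rho 0.3, 28% at 0.5, 13% at 0.7, 7% at 0.8 and 1% at 0.9. It also passes a share (1 − rho) of any T1 imbalance into the observed effect. The loss is material at moderate rho and negligible near 0.9, and the article does not say where rho lies. Independence is itself open to question, because the intervention is delivered in two groups of 10. The consequence is a wider and less stable effect estimate for planning the later trial. The absence of any between-arm test in the named procedure is a separate and larger fault in the same sentence, and one model can repair both.

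**What to change.** In 'Quantitative Analyzes' and in the Abstract's Methods, replace the comparison of raw change with a linear model of the T2 score on arm, with the same scale's T1 score as covariate. Apply it to the Recovery Assessment Scale, the Citizenship Measure, the COVID-19 Stress Scales and each repeated clinical recovery scale. Report the adjusted arm difference with its 95% CI as the effect estimate, and keep mean change per arm as descriptive.

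The change is a sentence of wording and a standard regression on data already collected, with no extra participants or visits. It uses one residual degree of freedom per outcome. It carries a very small precision loss if rho exceeds about 0.93 (20 v 10), 0.90 (17 v 7) or 0.83 (10 v 5 diagnostic comparisons).

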#### Allocation

Upon reception of the signed Information and Consent forms by email, consecutive referrals will be randomly allocated by computer algorithm to one of the two modalities at point of entry into the study on acceptation into the protocol using a computerized program (eg, randomization.com). At this entry point, the participant will have been evaluated, diagnosed, met inclusion criteria, and given formal consent for the randomization procedure. To ensure a balance in the allocation for the strata and thus control the risk of a secular trend in the composition of groups, random block sizes in a random order will be used (3, 6, 9, etc). Participants will thus be randomly allocated to the trial arm (n=20, 2 groups of 10) or control arm (n=10), and will be identified by a randomly assigned identification number. Among those allocated to the experimental groups, 10 patients with psychotic disorders will be randomly selected to be part of the transitional support group for patients with psychotic disorders, and 10 patients with anxiety or mood disorders will be randomly selected to be part of the transitional self-help group for patients with anxiety or mood disorders. It will be the same for the control group; 5 patients with psychotic disorders will be randomly selected to be part of the control group for patients with psychotic disorders, and 5 patients with anxiety or mood disorders will be randomly selected to be part of the control group for patients with anxiety or mood disorders. In both cases, those who have not been selected will be placed on a substitute list in the event of withdrawal of a selected patient, who will be replaced at random by one of the corresponding substitutes.

The groups will be studied together and separately: the experimental group for patients with psychotic disorders (n=10) will be compared to the control group for patients with psychotic disorders (n=5); the experimental group for patients with anxiety or mood disorders (n=10) will be compared to the control group for patients with anxiety or mood disorders (n=5); and the combined experimental group for patients with psychotic disorders and for patients with anxiety or mood disorders (n=20; 2×10) will be compared to the combined control group for patients with psychotic disorders and anxiety or mood disorders (n=10).

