**Figure 2 figure2:**
[figure not shown]
Weekly variations in new registrants to the MOOC (massive open online course) during the first 20 weeks of 2020. WHO: World Health Organization.

In 2017, before the current COVID-19 crisis, Bendezu-Quispe and colleagues [114] suggested that the emergence and re-emergence of communicable infectious diseases like Ebola or Zika were already increasing the necessity of knowledgeable and skilled health professionals, specifically with MOOCs arising as opportunities that allow people around the world to participate in higher-education courses. They argued that MOOCs can be used to learn about health issues of global relevance, and with the necessity of fast divulgation of knowledge and skills. Given the scope of mental health problems and the constraints of resources in training psychiatrists and other mental health professionals in most parts of the world, continuing education for medical and health or social services professionals and students, including in primary care, is vital [115]. In this MOOC, PSWs are included as training partners, as well as a subgroup of colearners.

Moreover, millions of people worldwide experienced moderate to severe levels of stress- or anxiety-related symptoms in response to COVID-19. This is true for the general population [116] as well as for people already diagnosed with psychotic disorders [117] or anxiety and mood disorders [118]. Yet, if general conditions remain the same for the participants of the experimental groups and for those of the control groups, and significantly different benefits are still observed among these groups, these differences will, in principle, be attributable to the intervention and not to the pandemic context.

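### The outcome test named, a paired t test run on each arm separately, cannot make the intervention-versus-control comparison the protocol intends, and no valid test or interval for the difference is specified

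*Protocol article*

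**What the plan says.** The Quantitative Analyzes section names a single outcome test: "We will compare within-patient change from baseline to intervention versus control group in the study outcome measures using the Student paired sample" t test. The Methods paragraph of the Abstract repeats it: "Changes will be compared between groups from baseline to endpoint in the intervention and control groups using the Student paired sample t test".

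The Quantitative Analyzes section then adds two sentences. The first splits the analysis by arm: "The analysis will run on intervention and control practices separately so as to explore practice level impact on the differences in outcomes". The second is the only between-arm procedure described: "Comparison of confidence interval and effect size between groups will be assessed". The analysis set is those with both time points: "All participants with data at baseline (T1) and follow-up will be included in the analyses".

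The Allocation section fixes the design: "Participants will thus be randomly allocated to the trial arm (n=20, 2 groups of 10) or control arm (n=10"). It promises three between-arm comparisons, namely 10 v 5 within each diagnosis group and the combined 20 intervention patients, who "will be compared to the combined control group for patients with psychotic disorders and anxiety or mood disorders (n=10").

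The Discussion states what will be concluded. If general conditions stay the same in both arms and "significantly different benefits are still observed among these groups, these differences will, in principle, be attributable to the intervention" rather than to the pandemic context.

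**The concern.** A paired t test needs two measurements on the same person. It can test T1 against T2 within the intervention arm, or within the control arm. It cannot compare 20 people with 10 different people. The sentence that runs the two arms separately confirms that the test would be applied arm by arm.

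The conclusion the study wants is a between-arm one. In a pandemic, a change common to both arms is plausible: restrictions ease, people recruited at a bad time drift back toward their average, and questionnaires are repeated. Within-arm tests cannot separate such a shared change from an effect of the peer support groups. With 2:1 allocation the larger arm is also more likely to reach significance when both arms change by the same amount.

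The word practices does not fit a trial that randomises individual patients at one institution. It may loosely mean the care given in each arm, and it is not a separate error.

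**Working it through.** **No figure to reproduce.** The protocol states no alpha, power, effect size or rule for declaring benefit. The two readings below are therefore assumptions, used to show what the gap could cost.

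**Inputs.**
- Planned arms: 20 and 10; within each diagnosis, 10 and 5 (Allocation).
- T2 completers in Table 1: intervention 7 + 10 = 17 of 20; control 7 of 10.
- Assumed: two-sided 5%, normally distributed change scores, and the same SD of change in both arms. Shared change d is in units of that SD, which the protocol does not give.

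**Reading A: significant improvement in intervention, no significant change in control.** With the same true change d in both arms there is no intervention effect, and the arms are independent, so

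P(false benefit) = P(intervention arm significant for improvement) × [1 − P(control arm significant)].

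Each probability is the power of a paired t test: noncentral t with n − 1 degrees of freedom and noncentrality d√n.

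- d = 0, any of the sizes: 0.025 × (1 − 0.050) = 0.024.
- d = 0.5, 20 v 10: 0.564 × (1 − 0.293) = 0.40.
- d = 0.615, 20 v 10: 0.742 × (1 − 0.412) = 0.436, the maximum.
- d = 0.73, 17 v 7: 0.807 × (1 − 0.369) = 0.509, the maximum.
- d = 0.98, 10 v 5: 0.787 × (1 − 0.389) = 0.481, the maximum.

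| Shared change d | 20 v 10 | 17 v 7 | 10 v 5 |
|---|---|---|---|
| 0 | 2.4% | 2.4% | 2.4% |
| 0.2 | 12% | 11% | 8% |
| 0.4 | 32% | 29% | 18% |
| 0.6 | 44% | 47% | 32% |
| 0.8 | 36% | 50% | 44% |
| 1.0 | 20% | 39% | 48% |

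With equal arms the maximum is 25%, so the unequal allocation adds to the problem.

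For scale, the Recruitment section gives a cross-sectional SD of 0.78 for the Recovery Assessment Scale mean. If the T1–T2 correlation ρ lies between 0.3 and 0.8 (assumed), the SD of change is 0.78 × √(2(1 − ρ)), which is 0.92 to 0.49. A change of 0.615 SD is then about 0.57 to 0.30 points on the 1-to-5 scale.

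**Reading B: the two arms' separate 95% intervals do not overlap.** Simulation with at least 100,000 runs per setting:
- Equal true change: non-overlap in favour of intervention in 0.3% to 0.4% of trials, and in about 0.7% counting both directions, at all three sizes.
- True difference of 1.0 SD: non-overlap in 36% of trials at 20 v 10 and 23% at 17 v 7.

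**Comparator: two-sample t test on change scores.** Its false-positive rate is 4.9% to 5.0% by simulation at all three sizes, because a shared change cancels in the difference. Its power for a true 1.0 SD difference is 70% at 20 v 10 and 57% at 17 v 7.

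**The case against.** The strongest reply is that the protocol does set out to compare the arms. The Abstract says so, the Allocation section lists three comparisons, and the analysis section ends with confidence intervals and effect sizes compared between groups. A reader might infer from the paired test that no between-arm comparison is planned at all. The documents do not support that: the comparison is intended, and what is missing is a valid way to make it.

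A reader might also take 44% as this plan's false-positive rate. It is not. No alpha is stated, and nothing says that significance in one arm and not the other will count as benefit. The Discussion speaks of benefits that differ between groups. Under Reading B the error runs the other way, toward low power. Nor is 44% a ceiling, since the completers reach 51%, or typical, since the rate is 2.4% with no shared change. Likewise, a shared trend can appear as an effect in the intervention arm only, but it will not always do so.

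These points limit the size of the claim. They do not rescue the named test. The unspecified comparison of intervals does not say whether they are per arm or for the difference, and neither reading tested above is sound. A separate analysis plan would not settle it either, because the protocol states an unsuitable test in two places. The feasibility label does not remove the problem, since the Discussion still draws a causal conclusion from group differences.

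**Conclusion.** The concern holds in this form: a between-arm comparison is intended, the only outcome test named cannot make it, and no valid test or interval for the difference is specified. The attribution in the Discussion is unsupported by the stated analysis.

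The mismatch itself rests on no assumption. Its numerical cost does: two-sided 5%, equal SDs of change, and one of two decision rules that the protocol does not state. Depending on the rule and the shared change, the cost is either false benefit well above 5% or roughly half the power of a proper test. The correction should be made before any between-arm conclusion is reported.

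**What to change.** In the Abstract (Methods) and in Quantitative Analyzes, replace the paired t test with one between-arm estimate per outcome: regress the T2 score on arm, T1 score and diagnosis group (psychotic v anxiety or mood), and report the adjusted difference with its 95% CI. A two-sample t test on change scores would also be valid; the choice between them is one of preference. State the alpha and sidedness. Keep within-arm changes as description only. Delete or reword the sentence on analysing practices separately, and say that the interval reported is the one for the difference.

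This needs no extra patients or data. It is not free of consequence, though: Table 1 already reports T2 completion, and Table 2 places the data analyses in December 2020. The change should be dated and disclosed as made after T2 collection, with a statement of whether outcome data had been examined by arm.
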